## Abstract

**Background:**

Between 2012–2022 opioid-related overdose deaths in the United States, including Washington State, have risen dramatically. Opioid use disorder (OUD) is a complex, chronic, and criminalized illness with biological, environmental, and social causes. One-fifth of people with OUD have recent criminal-legal system involvement; > 50% pass through WA jails annually.

Medications for Opioid Use Disorder (MOUD) can effectively treat OUD. WA has prioritized improving access to MOUD, including for those in jails. As patients in jail settings are systematically marginalized due to incarceration, it is critical to foster connections to MOUD services upon release, an acknowledged period of high overdose risk. Currently, there is insufficient focus on developing strategies to foster linkages between jail-based MOUD and referral services.

The *Systems Analysis and Improvement Approach (SAIA)*, an evidence-based implementation strategy, may optimize complex care cascades like MOUD provision and improve linkages between jail- and community-based providers. SAIA bundles systems engineering tools into an iterative process to guide care teams to visualize cascade drop-offs and prioritize steps for improvement; identify modifiable organization-level bottlenecks; and propose, implement, and evaluate modifications to overall cascade performance. The SAIA-MOUD study aims to strengthen the quality and continuity of MOUD care across jail and referral clinics in King County, WA, and ultimately reduce recidivism and mortality.

**Methods:**

We will conduct a quasi-experimental evaluation of SAIA effectiveness on improving MOUD care cascade quality and continuity for patients receiving care in jail and exiting to referral clinics; examine determinants of SAIA-MOUD adoption, implementation, and sustainment; and determine SAIA-MOUD’s cost and cost-effectiveness. Clinic teams with study team support will deliver the SAIA-MOUD intervention at the jail-based MOUD program and three referral clinics over a two-year intensive phase, followed by a one-year sustainment phase where SAIA implementation will be led by King County Jail MOUD staff without study support to enable pragmatic evaluation of sustained implementation.

**Discussion:**

SAIA packages user-friendly systems engineering tools to guide decision-making by front-line care providers to identify low-cost, contextually appropriate health care improvement strategies. By integrating SAIA into MOUD care provision in jail and linked services, this pragmatic trial is designed to test a model for national scale-up.

**Trial registration:**

ClinicalTrials.gov NCT06593353 (registered 09/06/2024; https://register.clinicaltrials.gov/prs/beta/studies/S000EVJR00000029/recordSummary).

**Supplementary Information:**

The online version contains supplementary material available at 10.1186/s13012-024-01409-0.

Contributions to the literature
Our study examines whether the introduction of an evidence-based, user-friendly, low-cost package of systems engineering tools can optimize investments in providing medications for opioid use disorder for individuals during the high-risk period immediately after exiting jail.This is the first application of the Systems Analysis and Improvement Approach (SAIA) across health system levels to optimize both care delivery and continuity of care.Our study is designed to provide decision-makers with evidence they need to decide whether to invest in systems engineering approaches during the expansion of MOUD in jail settings, including information on acceptability, feasibility, effectiveness and cost.

## Background

Over the last decade opioid overdose deaths have increased across the United States, including in Washington State (WA), where overdose accounted for 36% of all injury deaths in 2022 [1]. In King County, the most populous county in WA, opioid-related deaths doubled between 2020 and 2023 [2]. Overdose, especially related to opioids, is the leading cause of death for people who have been incarcerated [3, 4]. Immediately after release from carceral settings, individuals with OUD are at greatly increased risk for fatal opioid overdose [5, 6]. Structural racism compounds harms related to opioid use and incarceration, as generations of racist policies and practices disproportionately criminalize communities of color and social determinants of health impede access to opioid use disorder (OUD) prevention, harm reduction, and treatment [7–9]. As a result, Black, Hispanic, American Indian, and Alaska Native communities have experienced sharper increases in opioid overdose deaths, compared to white communities [10, 11].

Treatment with evidence-based agonist medications for opioid use disorder (MOUD), including buprenorphine and methadone, are effective for preventing overdose, [12–14] managing OUD, [15] and preventing recidivism [16]. The steps required to manage OUD are collectively known as the MOUD cascade of care and include living with undiagnosed OUD, OUD diagnosis, engagement in care, initiation of MOUD, long-term retention in care, and remission [17]. Despite common misconceptions that people who use drugs are not interested in clinical management of OUD, many patients using opioids want to quit or reduce their intake. A 2019 survey of WA residents utilizing syringe service programs showed that, of patients who mainly use heroin, 82% wanted to reduce or stop use and 70% were interested in MOUD [18]. With increasing recognition of the importance of social determinants of health like secure housing, adequate income, and food security on health outcomes, evidence suggests that patients on MOUD may have better outcomes with greater integration of clinical treatment and interventions targeting the social determinants of health [19]. This is especially relevant among individuals exposed to incarceration and at heightened risk for overdose. Settings such as jails must therefore engage people in a MOUD care cascade tailored to their setting, [20] including steps such as providing options for treatment with MOUD, administering MOUD, providing connections to recovery-supportive social services and connecting patients to clinical referral sites upon release. Completion of all cascade steps is necessary to reduce incarcerated patients’ risk of overdose and break cycles of incarceration.

There is a critical gap in knowledge surrounding implementation strategies to improve adoption, equity, and sustainment of MOUD care cascade services in jails and linked referral clinics in the community. There is an unprecedented influx of resources in WA and nationally being directed toward implementing MOUD, referring patients on MOUD to other services during care coordination visits, and ensuring that patients are connected to MOUD upon release [21]. However, there are limited resources and attention targeting development of evidence-based implementation strategies to optimize the MOUD care cascade between carceral settings and referral clinics upon release. Carceral settings are harmful to health and often not structurally aligned with the provision of respectful healthcare [22, 23]. Thus, implementing therapeutic interventions such as MOUD in jails requires tailored strategies to address challenges that are unique to these settings. To most effectively reduce opioid overdose risk—among other harms related to criminal legal system involvement [23]—the use of incarceration should be reduced or eliminated. It is therefore critical to focus improvements on linkages to post-release services to align with public health strategies to divest from OUD criminalization. Implementation strategies that address systemic weaknesses in MOUD services between carceral settings and referral clinics are therefore urgently needed.

Evidence-based systems-level implementation strategies like the *Systems Analysis and Improvement Approach* (SAIA) [24–26] improve care cascade efficiency, communication and accountability between providers, promote consensus decision-making in complex systems, and are potentially scalable across public health systems [27–34]. Though routine data exist to guide improvement efforts across varied clinical cascades, frontline providers are rarely engaged in the use of data to guide facility-level decision-making. Systems engineering methods utilize this data and systems thinking to 1) identify the main drivers for inefficiency across care cascades, 2) support provider decision-making to prioritize interventions, and 3) improve integration of services to meet the diverse clinical needs of patients [25, 28, 35]. SAIA bundles systems engineering tools into an iterative implementation strategy [35] designed to optimize multi-step complex cascades, such as the MOUD cascade across the jail-to-referral clinic continuum [25]. SAIA may be a vital strategy to address critical weaknesses in MOUD delivery systems for marginalized patients in King County, WA, and nationally.

SAIA-MOUD aims to make healthcare services more efficient and equitable across jail-based MOUD programs and clinical referral sites so that OUD care for patients leaving jail will be more continuous, equitable, and of higher quality. This may improve linkages to MOUD referral clinics and retention in care following release, ultimately improving OUD-related health outcomes, reducing criminal legal system involvement, and preventing overdose mortality. By focusing improvement efforts on the critical linkages between carceral settings and MOUD referral clinics, SAIA has the potential to create more responsive systems at a vulnerable moment in patients’ social context. Realizing the aims of SAIA-MOUD may create a scalable model for strengthening MOUD care between jail and referral clinics.

## Goals and objectives

The overall goal of this study is to strengthen the quality and continuity of MOUD care across jail and community settings in King County, WA by applying and evaluating a multi-component implementation strategy – the SAIA. Our population of interest are individuals who take MOUD during incarceration in King County, WA jails (JHS) and are subsequently referred to MOUD clinics in the community upon release. We hypothesize that organizations exposed to the SAIA will actively identify modifiable barriers to completing steps in the MOUD cascade and apply locally defined innovations that will lead to measurable improvements in the care and continuity of MOUD services for their patients over and above those observed in patients referred to MOUD clinics not exposed to the SAIA intervention. Over the five-year project, we will conduct a quasi-experimental evaluation of the effectiveness of SAIA on improving MOUD care cascade quality and continuity for patients receiving care in jail and exiting to referral clinics (Aim 1); examine determinants of SAIA-MOUD adoption, implementation, and sustainment (Aim 2); and determine SAIA-MOUD’s cost and cost-effectiveness (Aim 3).

## Methods

### Description of the SAIA-MOUD implementation strategy

The SAIA strategy bundles systems engineering tools into an iterative, five-step process applied at the facility-level to give frontline workers and managers a systems view of cascade performance, identify priority areas for improvement, discern modifiable barriers, and test workflow modifications and has been previously described in the literature (Fig. 1). Procedures for the adapted SAIA-MOUD’s five steps include:

**Fig. 1 Fig1:**
[figure not shown]
SAIA-MOUD overview

#### Step 1: Understand MOUD performance and identify priority areas for improvement

The MOUD Cascade Analysis Tool (MCAT) uses routine data to provide a rapid view of drop-offs along the MOUD cascade. Two MCATs have been developed and refined for this study. As an analytic tool, the jail-level MCAT provides care staff with a view of the greatest potential for flow improvements through OUD screening➔MOUD referral➔MOUD access➔release on MOUD as well as linkages between jail and MOUD referral clinics (Fig. 2a). Facilitative sub steps including client’s receipt of an exit interview, referral to community-based MOUD clinic, and/or MOUD prescription or carry medication, are captured but do not contribute to the cascade analysis calculation. The clinic-level MCAT offers health teams a view of the greatest potential for flow improvements for individuals exiting jail on MOUD within 30 days through MOUD evaluation➔ MOUD prescription➔ MOUD pick up/administration➔ follow up visit within 30 days of first visit➔ MOUD pick up/ administration (at second visit) (Fig. 2b).

**Fig. 2 Fig2:**
[figure not shown]
**a** JHS MOUD cascade analysis tool (MCAT). **B** Clinic MOUD cascade analysis tool (MCAT)

#### Step 2: Identify facility-level modifiable bottlenecks using process mapping

Enabling facility staff to identify and gain consensus on specific bottlenecks to address in their MOUD care system is essential to defining innovations to implement. The SAIA applies sequential process flow mapping (Fig. 3.), [24] coupled with workflow observation, to identify bottlenecks and guide discussion on workflow modifications across MOUD services.

**Fig. 3 Fig3:**
[figure not shown]
Ex, jail-based process map

#### Step 3: Define and implement facility-specific workflow adaptations to address modifiable bottlenecks

After identifying modifiable barriers within cascade steps, facility staff select a specific change to improve performance. Selected workflow adaptations should be within the scope of influence of facility management and staff, feasible to implement, and expected to lead to rapid, substantial improvements in the targeted cascade step. Ideas for adaptations come from brainstorming solutions with facility-level staff, best practices from high performing MOUD services and published literature. Changes can be structural (e.g. re-purpose or modify consult rooms, alter staffing patterns), or process-oriented (e.g. modify visit schedules, engage partners in MOUD, enhance stigma reduction counseling). A workplan for the innovation (‘micro-intervention’) is developed by facility personnel to ensure consensus, delineate the MOUD cascade step and bottleneck addressed, and clarify operational design and roles.

#### Step 4: Monitor changes in performance and adopt / adapt / abandon

Facility staff monitor improvements in MCAT performance from the micro-intervention by measuring the increase in the proportion of patients progressing through targeted steps. Based on results, facility staff decide to adopt the change as standard practice, adapt and re-test the modification, or abandon it.

#### Step 5: Repeat cycle

Systems engineering process improvements are iterative, with ongoing testing of innovations responsive to evolving, contextually specific barriers. Facility staff repeat steps 1–4 at the end of each cycle, focusing on identifying new approaches to modify previously identified barriers, or if the first cycle was successful, testing micro-interventions to new bottlenecks identified in a repeated systems analysis.

### SAIA-MOUD trial design

Using a three-year quasi-experimental design, we will prospectively evaluate the effectiveness of SAIA-MOUD on improving MOUD care cascade quality and continuity for patients receiving care in jail and exiting to referral clinics in King County, WA (StaRI Checklist, Additional file 1) [36]. Clinic teams with support from the study team will deliver SAIA-MOUD at the jail-based MOUD program and three referral clinics over a two-year intensive phase, followed by a one-year sustainment phase where SAIA implementation will be led by JHS and MOUD clinic managers without study personnel support to enable pragmatic evaluation of sustained implementation (Table 1). The trial will culminate in a dissemination package, summarizing trial results and providing implementation and cost guidance to support state-level SAIA-MOUD scale-up. The mixed-methods evaluation will assess the impact of SAIA-MOUD on patient-level outcomes (Table 2).

**Table 1 Tab1:**
[figure not shown]
SAIA-MOUD study timeline

Key: SAIA-MOUD: Systems Analysis and Improvement Approach for the Medications for Opioid Use Disorder Care Cascade, *UW* University of Washington, *IRB* Institutional Review Board, *WA* Washington, *SOPs* Standard Operating Procedures, *MCAT* MOUD Cascade Analysis Tool

**Table 2 Tab2:** SAIA-MOUD study outcomes

	**Outcome**	**Indicator**	**Numerator**	**Denominator**
Primary	Linkage	MOUD receipt ≤ 30 days of jail release	# of patients on MOUD in jail who upon release receive MOUD at a referral clinic ≤ 30 days	# of patients on MOUD in jail and released to the community
Secondary	Retention	MOUD receipt ≤ 30 days of initial linkage	# of patients on MOUD in jail who link to MOUD services upon release and subsequently return for a second receipt of MOUD ≤ 30 days	# of patients on MOUD in jail who upon release receive MOUD at a referral clinic ≤ 30 days

Covariates: sex, race, ethnicity, housing stability

### Process for introducing SAIA

SAIA-MOUD’s standard operating procedures (SOP) including the timing/duration, training schedules and intervention component guidelines (MCAT, process mapping and CQI) have been developed and acceptability tested with frontline MOUD staff and managers in the proposed study setting as part of formative work. In the first month of intervention, each facility team (including managers and staff from a range of sectors) will receive an on-site, 2-day orientation from the study team on the SAIA-MOUD SOPs. During this orientation to SAIA-MOUD implementation, facility teams jointly populate and interpret the MCAT, develop process maps of current patient care pathways to initiate or continue MOUD at their sites or referral clinics, and define 1–2 micro-interventions, and indicators to monitor the impact of these modifications.

In the first month of the SAIA-MOUD trial, each facility team will receive two 60-min supervision visits by study personnel, followed by monthly visits throughout the remainder of the 24-month intensive implementation period. During the 12-month sustainment period monthly mentorship visits will be conducted internally by the site team without support from study personnel to evaluate SAIA-MOUD sustainment with moderate resource investment.

Based on the other SAIA adaptations and the development process of the MCAT and its beta testing, we expect that analysis and improvement cycles will occur monthly, with an average of 12 cycles per year per implementing facility.

### Study setting

Our study will be conducted in King County, the most populous county in Washington State (WA), which reports rising rates of opioid-related overdose and high prevalence of OUD in carceral settings [21]. The SAIA-MOUD intervention will be introduced in four sites — 1) King County Jail Health Services (JHS) which is co-located across two jail-based clinics (King County Correctional Facility’s (KCCF) and Maleng Regional Justice Center’s (MRJC) MOUD program), Harborview Medical Center’s Opioid Treatment Network (HMC-OTN) (co-located across five clinic service points), Pathways Clinic, and Sound Health. With the exemption of the MRJC, which is in Kent, WA, all SAIA-implementing sites are based within walking or easy bus-ride distance of one another in central Seattle, where the majority of opioid overdoses occur in King County [1].

JHS has been a provider of MOUD since 2008, when methadone continuation was authorized. Ten years later, in June 2018, buprenorphine continuation was offered to inmates with existing prescriptions. In 2020, a pilot of buprenorphine initiation was conducted in JHS, and in 2021 it was integrated as part of a broader coordinated enhanced discharge program, making JHS an early-adopter of jail-based MOUD provision in the state [37]. JHS is one of the largest jails in Washington, housing ~ 1200 incarcerated people (approximately 10% of Washington’s jailed population) daily [38]. JHS provides MOUD services to ~ 150 patients on any given day; [37] however, gaps in the hand-off between jail and MOUD clinical services upon patients’ release contribute to unacceptable levels of opioid overdoses at this high risk “in-between” time.

HMC-OTN (a UW-affiliate), Pathways (a PHSKC-affiliate) and Sound Health (a community-based mental health non-profit organization) are similarly patient-centered, low barrier clinics, designed to be most accessible for marginalized populations, such as those exiting jail. All community-based clinics offer wrap-around services, including referrals to services that meet patient-identified, non-clinical needs, including housing, food and job-seeking supports. According to clinic managers each clinic sees ~ 150–350 MOUD patients monthly, including approximately 5–10% who are exiting JHS, and most staff have been employed for at least two years.

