#### Data sources

Multiple routine data sources will be used to measure our effectiveness outcomes, which are routinely integrated into the Integrated Data Hub (IDH) which is housed jointly by Public Health—Seattle & King County (PHSKC) and King County’s Department of Community and Health Services. The IDH includes data from multiple sources of interest – including the Medicaid payer system (for which over 93% of those leaving JHS are eligible), jail booking data, and Homelessness Management Information System. With approval from the WA State Department of Health, both the Prescription Monitoring Program (PMP), and mortality data will be linked to the IDH data using a PHSKC machine learning approach, developed for another study. Data from the IDH will be cross-checked with clinic data reports generated through the EPIC system on a quarterly basis to assess data availability and completeness. Inconsistencies will be explored at the site level.

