#### Data analysis

For our primary linkage outcome we will measure the change in proportion of clients linked in two ways: 1) a difference in proportions test comparing the average share of clients linked in the baseline period to the average share of clients linked in the intervention period and 2) a non-parametric interrupted time series (ITS) analysis. For the ITS, the proportion of clients linked will be aggregated quarterly, and the model will be adjusted for covariates including sex, age, race, ethnicity and housing status at jail release, treatment experience prior to incarceration in jail and form of MOUD provided in jail.

For our secondary analysis on retention in care, patients initially linking to SAIA clinics will be matched to patients initially linking to non-SAIA clinics using propensity score matching. Variables used in the propensity score will include sex, age, race, ethnicity and housing status at jail release, treatment experience prior to incarceration in jail and form of MOUD provided in jail, in addition to the baseline period retention rate of the index provider seen following release. Our primary approach will rely on inverse probability weighting with the estimated propensity scores. We will also assess the robustness of our results using a kernel-density-based matching estimator using the propensity scores. Our estimate of interest is the average treatment effect on the treated (ATT).

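### Releasing jail is not among the named propensity-score variables for the retention comparison, although the protocol itself places one of the two jails away from the SAIA clinics

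*Protocol article*

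**What the plan says.** The Study setting section counts the jail health service as one of the four SAIA sites: "King County Jail Health Services (JHS) which is co-located across two jail-based clinics", KCCF and MRJC. It then singles out one of the two by location: "With the exemption of the MRJC, which is in Kent, WA, all SAIA-implementing sites are based within walking or easy bus-ride distance".

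For retention, the Data analysis section states that "patients initially linking to SAIA clinics will be matched to patients initially linking to non-SAIA clinics using propensity score matching". It plans inverse probability weighting as the main approach and the average treatment effect on the treated as the estimate. "Variables used in the propensity score will include sex, age, race, ethnicity and housing status at jail release", followed by earlier treatment experience, the form of MOUD given in jail, and the index provider's retention rate in the baseline period.

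For linkage, the first analysis is "a difference in proportions test comparing the average share of clients linked in the baseline period" with that in the intervention period. It has no covariates or strata. The second is an interrupted time series (ITS), where "the model will be adjusted for covariates including sex, age, race, ethnicity and housing status at jail release", plus earlier treatment experience and form of MOUD.

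The note under Table 2 reads "Covariates: sex, race, ethnicity, housing stability". The cost-effectiveness subgroups are implementation year and those same four factors. Releasing jail is in none of these lists. The Data sources section says the Integrated Data Hub holds "jail booking data, and Homelessness Management Information System" data, among other sources.

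**The concern.** A propensity score should contain variables that precede treatment and may influence both the group a patient falls into and the outcome. Here the group is the clinic a patient first links to. All three SAIA clinics are in central Seattle, as is KCCF; MRJC is in Kent. The protocol thus supplies the reason to expect releasing jail to predict clinic choice. If releasing jail also relates to return within 30 days, through travel or through where people live after release, leaving it out lets geography enter the SAIA versus non-SAIA contrast.

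The primary outcome is exposed to a narrower form of the problem. The powered test pools the two jails in each period. A change in the share of releases from MRJC between 2022–2023 and the intervention period would move the pooled proportion if linkage differs by jail.

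**Working it through.** **The plan's own yardstick.** Inputs from the Power and sample size section: baseline linkage 22%, 2,400 releases per period. Two-sided alpha of 0.05 is assumed, as none is stated. With the variance held at baseline:

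- Standard error = √(0.22 × 0.78) × √(2/2400) = 0.4142 × 0.02887 = 0.01196.
- 80% power: (1.960 + 0.842) × 0.01196 = 3.35 points (stated: 3.3).
- 90% power: (1.960 + 1.282) × 0.01196 = 3.88 points (stated: 3.9).

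The stated figures are reproduced closely. The pooled-variance formula for an increase from 22% gives 3.44 and 4.00. The difference is small and does not bear on this point.

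**Retention: which named variable could carry releasing jail?**

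| Named variable | Does it balance patients by releasing jail? |
|---|---|
| Sex, age, race, ethnicity | Not directly |
| Housing status at release | In part, if it tracks location |
| Earlier treatment, form of MOUD | Not directly |
| Index provider's baseline retention | In part: a provider average, not a patient characteristic |

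**Retention: illustration only.** Every input is assumed: 30% of linkers leave MRJC; 70% of KCCF linkers and 30% of MRJC linkers use a SAIA clinic; retention depends on the jail and not on the clinic.

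- MRJC share of the SAIA group = 0.3 × 0.3 / (0.3 × 0.3 + 0.7 × 0.7) = 0.09/0.58 = 15.5%.
- MRJC share of the comparator = 0.3 × 0.7 / (0.3 × 0.7 + 0.7 × 0.3) = 0.21/0.42 = 50%.
- Crude false difference = (0.50 − 0.155) × (KCCF retention − MRJC retention).
- Retention 60% at KCCF and 50% at MRJC: 58.45% − 55% = about +3.4 points.
- The reverse, 50% and 60%: 51.55% − 55% = about −3.4 points.
- No retention gap by jail, or no link between jail and clinic choice: 0.

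These are unadjusted differences. In the first case, if the jail mix was the same at baseline, the SAIA providers' baseline retention would also average 58.45% against 55%. The same 3.4-point gap would then appear in a variable already in the propensity score, and weighting on it could remove much of the difference.

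**Linkage: algebra.** Let m1 and m2 be the MRJC share of releases at baseline and in the intervention period, with linkage pM and pK in the two jails and no SAIA effect. The pooled change is

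[m2·pM + (1 − m2)·pK] − [m1·pM + (1 − m1)·pK] = (m2 − m1) × (pM − pK).

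If m1 = m2, it is zero whatever the gap between jails. Within each jail the change is also zero, so a stratified risk difference removes the effect of mix. With assumed shifts and gaps, 2,400 per period and a 22% baseline:

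| Shift in MRJC share (points) | Linkage gap (points) | False change (points) | Chance of a significant result with no SAIA effect |
|---|---|---|---|
| 0 | any | 0 | 5% |
| 5 | 10 | 0.5 | 7.0% |
| 10 | 10 | 1.0 | 13.2% |
| 20 | 10 | 2.0 | 37.7% |
| 20 | 15 | 3.0 | 68.8% |

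Over shifts and gaps of 5 to 20 points each, the false change runs from 0.25 to 4.0 points. To reach the full 3.3 points, the mix must shift by 33 points at a 10-point gap (3.3/0.10), or by 16.5 at a 20-point gap (3.3/0.20).

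**The case against.** The strongest reply has four parts.

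- **The lists are open.** Both are introduced by a form of the word include, and this is a condensed article. That stands as a reason for moderation. But the article does name its variables in detail, down to a provider-level rate, and an open list does not commit anyone to adding the jail.
- **The retention mechanism is inferred.** The documents do not say where people live after release or where the non-SAIA clinics are. Someone released in Kent who links to a nearer clinic may return as readily as anyone else, and retention is measured only in people who have already linked. This stands: it is why no size or sign can be given. It does not remove the case for balancing a pre-treatment variable that plausibly drives clinic choice.
- **Provider baseline retention already absorbs much of a stable geographic gap.** This stands in part, as the illustration shows. Being an average, it does not balance individual patients by jail.
- **The primary analysis is not biased by a stable difference between jails.** This stands in full.

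A reader might infer more: that a jail difference as such can pass for a SAIA effect on linkage, that retention would show a false SAIA advantage of about 3.4 points, or that SAIA is delivered unevenly in the two jails. The documents support none of these. Both jails belong to one site and are pooled in both periods, no change in mix is reported, the 3.4 points is a crude figure from assumed inputs whose sign can flip, and nothing suggests uneven delivery.

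**Conclusion.** The point holds for the retention analysis. The protocol separates one releasing jail geographically from the SAIA clinics, compares patients by the clinic they reach, and does not name releasing jail in the propensity score. The variables it does name cover the gap only in part. How much bias remains, and in which direction, cannot be derived from the documents. The conclusion rests on two plausible but undocumented links: from releasing jail to clinic choice, and from releasing jail to return within 30 days.

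For linkage, the point is conditional. It matters only if the jail mix changes between 2022–2023 and the intervention period, which the documents neither report nor exclude, and only if linkage also differs by jail. A false change near the detectable 3.3 points needs both a large shift and a large gap. This justifies a sensitivity check but not a different primary test.

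**What to change.** 1. **Retention.** Add releasing jail (KCCF or MRJC) to the propensity score and report balance on it after weighting. First confirm that the jail data in the Integrated Data Hub record the facility of release: the article mentions only booking data, and the two facilities need not be the same.
2. **Linkage, pooled test.** Keep the planned difference in proportions as it is. Add, as a sensitivity check, a table of releases and linkage by jail and period with a Mantel-Haenszel risk difference stratified by jail.
3. **Linkage, ITS.** Add releasing jail to the covariates. This alone would not be enough, since it leaves the unadjusted pooled test unchanged.

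The cost is one binary variable and one extra table, with no new data collection if the facility of release is recorded. If the jail predicts clinic choice but not retention, the weights become somewhat more variable and the retention estimate slightly less precise. The stated detectable change is unaffected, because the powered test stays unadjusted.
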